### Analysis (2): implementation evaluation

Descriptive analyses will be reported on frequencies of program intervention activities relative to plans, and participation levels in program activities.

Interview transcripts will be analysed using descriptive thematic analysis [26] to answer the following Research Questions:Was the MATES in Manufacturing program implemented as designed?What were the barriers and facilitators to participation in, and implementation of, MATES in Manufacturing?What were participant and staff experiences of the program, including any noted outcomes arising (positive, negative, or other)?

The suicide prevention literacy process measures collected by survey will be analysed as above for the quantitative effectiveness evaluation, Research Question 4:4)Was suicide prevention literacy increased by the MATES in Manufacturing program relative to wait list controls? (process evaluation)

### Analysis (3): economic evaluation

If the trial achieves significant positive improvements in the primary outcome of help-seeking intentions, a trial-based economic evaluation will be conducted based on the help-seeking intention scores, the intervention costs, and mental health-related services costs. Intervention costs include the intervention development costs (e.g. planning, development, and materials). Mental health services cost will be calculated by applying standard Australian unit costs (i.e. Independent Hospital Pricing Authority [27], Medicare Benefit Scheme fees [28]) to the resource use units collected through the HSUQ. Mean values of costs and help-seeking intention scores will be reported for both groups and assessed by generalised linear models. An incremental cost-effectiveness ratio (ICER) will be calculated as the difference in average cost between the groups, divided by the difference in help-seeking intention scores. Nonparametric bootstrapping will be used to obtain confidence intervals for incremental cost-effectiveness ratios. A modelled economic evaluation will also be undertaken using the results of this trial and relevant epidemiological literature to extrapolate long-term costs and consequences associated with help-seeking intentions.

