The following Research Questions (RQ) will be addressed using mixed methods for RQ 1–3 and quantitative methods for RQ 4–6:Was the MATES in Manufacturing program implemented as designed?What were the barriers and facilitators to participation in, and implementation of, MATES in Manufacturing?What were participant and staff experiences of the program, including any noted outcomes arising (positive, negative, or other)?Was suicide prevention literacy increased by the MATES in Manufacturing program relative to wait list controls? (process evaluation)Did intentions to seek help increase in the MATES in Manufacturing program relative to wait list controls? (primary outcome)Did help seeking behaviour increase, and levels of distress and suicidal ideation decrease, in the MATES in Manufacturing program relative to wait list controls? (secondary outcomes)

We also aim to evaluate the cost-effectiveness of the intervention if it is shown to have a significant positive effect on the primary outcome of help-seeking intentions.

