#### Data collection timing

Intervention sites will participate in baseline surveys then 8 months of the MATES in Manufacturing program from the first GAT on site, with follow-up surveys administered 8 months after intervention initiation. Wait-list control sites will participate in baseline surveys (month 0) then follow-up surveys 8 months later. At wait-list control sites, the MATES program will commence following the 8 month surveys, then continue for at least 8 months. See Fig. 2: schedule of enrolment, interventions, and assessments.

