#### Health service use (economic evaluation)

Health service use will be assessed using a modified version of the self-report measure of the Resource Use Questionnaire [23] developed for use in this study. Five questions will assess participants’ use of a range of health services for mental health difficulties over the preceding 6 months, including primary health services (e.g. consultations with a general practitioner, psychologist) and inpatient admissions (e.g. hospital, community care unit). Use of psychotropic medications (e.g. sleeping tablets, antidepressants) is also assessed, as is the effect of mental health difficulties on functioning at work and absence from work.

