### Analysis (1): quantitative effectiveness evaluation

The primary analysis will be undertaken on an intention-to-treat basis: including all participants as randomised, regardless of treatment received or withdrawal from the study. Mixed-model Repeated Measures (MMRM) analyses will be used because of the ability of this approach to include participants with missing data. Cluster effects will be modelled using a random site effect. An unstructured residual variance-covariance matrix will accommodate within-participant dependency. The statistical significance of the primary outcome will be evaluated in a planned comparison of change from baseline to 8 months post-initiation of intervention in the active arm compared to 8-month change in the waitlist group. Tests of significance will use appropriate degrees of freedom adjustment where necessary (i.e., the Kenward-Roger method based on the observed information matrix). Where necessary, transformation of the outcome variable will be undertaken to ensure distributional assumptions of the model are met.

For binary outcomes (prevalence of suicidal ideation) and other non-continuous outcomes (severity of suicidal thoughts and behaviours), comparable generalized mixed models will be used with population average effects of intervention being compared.

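### The economic evaluation runs only if the primary test is significant, and its 6-month service-use recall does not match the 8-month comparison

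*Protocol article*

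**What the plan says.** The condition appears twice in the protocol article. In the Introduction, after the research questions, cost-effectiveness is to be evaluated "if it is shown to have a significant positive effect on the primary outcome of help-seeking intentions". The section Analysis (3): economic evaluation repeats it: "If the trial achieves significant positive improvements in the primary outcome of help-seeking intentions, a trial-based economic evaluation will be conducted".

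That section defines the ICER as the between-group difference in average cost divided by the difference in help-seeking intention scores. The outcome that opens the gate is therefore also the denominator. On method it says "Mean values of costs and help-seeking intention scores will be reported for both groups and assessed by generalised linear models", and "Nonparametric bootstrapping will be used to obtain confidence intervals for incremental cost-effectiveness ratios". A longer-term model is then to be built on the trial results.

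On timing, the section Health service use (economic evaluation) asks about "use of a range of health services for mental health difficulties over the preceding 6 months". Data collection (1) places this questionnaire once, at 8 months, at both intervention and wait-list sites. Intervention description sets an 8-month program period within the study, and Data collection timing has intervention sites surveyed "with follow-up surveys administered 8 months after intervention initiation".

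On clustering, Analysis (1) states for the effectiveness analysis: "Cluster effects will be modelled using a random site effect". Analysis (3) does not mention sites.

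**The concern.** Whether an intervention is worth its cost does not depend on whether its effect passed a 5% test. A non-significant difference is not a zero difference, and the program costs are incurred either way. Under the stated rule a null or borderline trial yields no economic result, although the service-use data will have been collected in both arms. A reader of a published ICER would also be looking at a figure that could appear only if the estimated effect was large enough to be significant. The long-term model would inherit that selection.

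The recall period raises a different problem. The numerator of the ICER would combine intervention costs, which carry no 6-month limit, with service costs from only the last 6 months, and set both against an 8-month change in the outcome. At intervention sites the unobserved months are the first ones after the initial awareness training.

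**Working it through.** **Inputs.** From Power and sample size: alpha 0.05 (two-sided assumed, since the article does not say), power 0.80 (printed there as beta), d = 0.30, ICC 0.02 used and 0.0112 estimated, and 19, 14 and 10 sites at 30, 50 and 100 workers per site. From the economic and timing sections: 6-month recall, one survey at 8 months, 8-month program.

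**The plan's own figure.** Analysis (3) gives none, so I checked the sample size to confirm the design-effect method.
- Per arm: n = 2 × ((1.960 + 0.842)/0.30)² = 174.4, so 175, or 350 in total.
- Design effect: DE = 1 + (m − 1) × 0.02.
- m = 30: DE 1.58, 553/30 = 18.4, so 19 sites (agrees).
- m = 50: DE 1.98, 693/50 = 13.9, so 14 sites (agrees).
- m = 100: DE 2.98, 1043/100 = 10.4, so 11 sites against 10 stated. Power at 10 × 100 is 78.5% by the normal formula.

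The method is confirmed. The one-site difference does not bear on this point.

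**Significance gate.** Let θ be the true effect divided by its standard error. At 80% power θ = 1.960 + 0.842 = 2.802. The expected estimate given z > 1.960 is θ + φ(1.960 − θ)/power = 2.802 + 0.280/0.80 = 3.152.
- Ratio to truth: 3.152/2.802 = 1.125, so about 12% too high.
- The same formula gives 1.06 at 90% power, 1.13 at 78.5% and 1.41 at 50%.
- At 80% power, 1 − 1/1.125 = 11%. This is roughly how far an ICER evaluated at the inflated effect would fall below the truth, if incremental cost is positive and unrelated to the estimated effect.
- Chance of no economic result when d = 0.30 is true: 1 − 0.80 = 20%.

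**Recall window.** 6/8 = 75% of the period is observed, so 25% of service use is missed if the rate is constant. The article gives no cost figures. For illustration, assume an incremental intervention cost of 100 and a true 8-month service-cost difference D. The recorded total is 100 + 0.75D and the true total is 100 + D.

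| D | Recorded | True | Error in ICER |
|---|---|---|---|
| −50 | 62.5 | 50 | +25% |
| −20 | 85 | 80 | +6% |
| 0 | 100 | 100 | 0 |
| +20 | 115 | 120 | −4% |
| +50 | 137.5 | 150 | −8% |

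The direction depends on whether the program raises or lowers service use, which is unknown.

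**Clustering, only if workers were resampled singly.** The interval would be 1/√DE of its correct width. No ICC for costs is given, so the range for intentions is assumed.
- 100 per site, ICC 0.02: 1/√2.98 = 58%, with nominal 95% coverage of about 74%.
- 100 per site, ICC 0.0112: DE = 1 + 99 × 0.0112 = 2.11, 1/√2.11 = 69%, coverage about 82%.
- With 50 or 30 responders per site at ICC 0.02: 71% and 80% of the correct width.
- In a simulation with 5 sites per arm of 100 workers, a bootstrap of whole sites covered only about 88%.

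**The case against.** The strongest reply on the gate is that it is openly pre-specified, and that in a trial that passes it the ICER is the same number with or without the condition. That stands: deleting the condition does not remove the 12% from an ICER that would have been reported anyway. The gain is that an economic result also exists after a non-significant test, so reported results are no longer a selected set.

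On recall, both arms share the same window, and that also stands. A common window does not make a between-arm difference complete, but it is one reason why no direction of bias can be claimed.

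Several stronger readings are tempting, and the document does not support them.
- **That the economic methods ignore clustering and the interval is too narrow.** Analysis (3) is silent on this. A generalised linear model can carry cluster-robust errors, a bootstrap can resample sites, and a condensed article may leave this to an analysis plan that is not shown. The 58–69% figures are conditional. The economic questionnaire is also a voluntary QR-code supplement, so responders per site may be fewer than 100.
- **That only 6 of 8 program months are costed.** The window applies to self-reported service use, not to intervention costs.
- **That delivery costs are left out.** The article says intervention costs include development costs, which is not an exhaustive list.

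**Conclusion.** Two defects lie in the stated text and should be corrected.

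First, the significance condition leaves no cost-effectiveness estimate about 20% of the time at planned power even if d = 0.30 is true. It also means that any reported ICER comes from a set whose expected effect is about 12% too high. Both figures assume a two-sided 5% test and 80% power, and the inflation grows if true power is lower.

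Second, the 6-month recall at 8 months misses about a quarter of the service-use period in each arm, assuming a constant rate. A reader might infer that the ICER is biased in a known direction, but the recall gap gives none: over the assumed cost splits the error runs from +25% to −8% and includes zero. Only the gate has a predictable direction, and only where incremental cost is positive.

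The handling of sites is a request for an explicit statement, prompted by the contrast between Analysis (1) and Analysis (3). It is not a demonstrated error.

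**What to change.** - **Gate.** Delete the significance condition in the Introduction and in Analysis (3), and run the evaluation whatever the primary result. Report incremental net benefit with its uncertainty alongside the ICER, because the ratio becomes unstable when the effect is near zero. Net benefit needs a value per point of the help-seeking score. The article gives none, so show it over a range.
- **Recall.** Set the service-use recall to 8 months, as the Help sought section already does for forms of help sought. Otherwise state a 6-month service-cost horizon and either scale it to 8 months or test it in a sensitivity analysis.
- **Sites.** State that the cost and effect models include a site effect, and that the bootstrap resamples sites or is two-stage (sites, then workers). With about 10 sites, add a small-number-of-clusters correction, since plain site resampling under-covers.

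The cost is some analyst time and one changed number on the time-2 questionnaire, with no new data collection. The downsides are slightly longer recall and the possibility of publishing a less favourable or inconclusive economic result.

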### Ethics approvals and monitoring

Ethics approval for the cRCT was granted on 3 September 2021 by the Deakin University Human Research Ethics Committee (protocol number 2021–276), with approval for the qualitative implementation evaluation on 30 September 2022 from the Western Sydney University Human Research Ethics Committee (protocol number H14506). See Supplementary File 3 for Ethics Approvals. The research will be subject to compliance monitoring and auditing by these two university Ethics Committees. In addition, the lead investigator and MATES staff report biweekly on trial progress to the meeting of the joint labour-management Steering Group. The Steering Group was initiated in 2020, and the trial lead investigator has been participating since early 2021, in the lead up to site recruitment. Progress of the trial, implementation of intervention activities, and any concerns arising from participating company and union representatives and MATES staff are discussed. MATES reports on the uptake and usage of the MATES 1–800 and case management services (aggregate usage only, no company identifiers), and participating companies and unions report on their experiences of the trial and MATES program to date. We do not have ‘trial stopping’ guidelines in place, but do have a Withdrawal of Consent process for participating companies (see Supplementary File 1). These monitoring functions operate independently of the funder of the research. There is no trial sponsor and there is no formal Data Monitoring Committee; these were deemed unnecessary because this a community-based and not a clinical trial.

### Trial status (as of submission)

Site recruitment commenced in December of 2021, but has been hampered by the COVID-19 pandemic and the associated restrictions and impacts on businesses. As sites were recruited, they were grouped and randomly assigned as soon as feasible, such that data collection and intervention implementation could be spread out over time and managed with the small implementation and research teams available. Two groups of four sites have been recruited and baseline data collection completed before random assignment by the procedure detailed above (running total = 5 sites assigned to intervention and 3 sites to wait-list control). Intervention activities have been initiated at most sites assigned to the intervention condition. A third and final group of sites awaits completion of baseline surveys and random assignment. The 8 sites recruited to date vary widely in size, ranging from 25 up to 440 workers, corresponding to an estimated study population of 1573 workers in total. Survey participation to date has been relatively high, with an overall average of 74% and a range of 60–92% over the 8 sites.

Though few in number, distressed workers have been identified and followed up while piloting the survey, and at both intervention and wait-list control sites during the conduct of baseline surveys; the frequency and nature of these events will be captured from Field Officer notes. While strictly speaking, this would constitute ‘contamination’ of wait-list control sites, this is a limitation that is ethically imperative and is not likely to affect the overall results of the trial.

### Dissemination

For study participants, the final results of the trial RCT will be presented to the joint labour-management Steering Group, and we will provide a plain English lay summary for distribution to program participants by management and union steering group members. For the research, policy, and practice communities, we will publish peer-reviewed journal articles and deliver presentations at national and international research conferences. We will also deliver other presentations on findings to mental health and suicide prevention practitioners and policymakers.

## Discussion

This project represents a strong partnership bringing together practitioners at the coalface of suicide prevention (MATES), industry partners (participating sites, unions, and Steering Group), and suicide prevention researchers. Further, the trial addresses an urgent need for experimental evidence on the effectiveness of workplace suicide prevention programs, both for MATES in particular as well as for workplace suicide prevention in general [29]. The qualitative implementation evaluation aims to provide narrative insights into how the intervention gets implemented: what it “looks like” in practice [30]. The qualitative implementation evaluation will be complemented by quantitative data collection focussed on the extent to which program components were implemented as planned as well as the extent of participation in intervention activities. The combination of qualitative and quantitative methods will enable the exploration of context-specific factors that could modify intervention implementation as well as effectiveness [31].

While the cRCT design provides strong internal validity, our study may be limited with respect to external validity, or generalisability. Worksites that have engaged with the labour-management steering committee and are willing to accept the terms of an experimental study may be a select group that is not representative of all manufacturing worksites. Within sites, however, we expect that the potential for selection bias is limited, given the relatively high participation rates in the baseline surveys (average = 74%), which we will hope to retain at follow-up.

In addition to contributing to the international literature on workplace suicide prevention, the trial will generate evidence-based policy and practice insights for the partners involved. The MATES intervention is being implemented under real world conditions by an established workplace suicide prevention charity, driven by a need identified by industry partners; hence the potential for translation of this research to policy and practice is high. The project partners are well positioned to adapt and disseminate findings to a wide range of workplace mental health and suicide prevention stakeholders. The MATES workplace suicide prevention strategy under evaluation could also be adapted to other settings nationally and internationally if the findings are positive, and at a minimum will provide implementation and effectiveness insights for future research, policy and practice.

## Data Availability

The datasets used in the current study are available from the corresponding author on reasonable request. Anonymized, participant-level data may be made available to external researchers on the basis of a scientifically sound proposal, subject to ethics approval. The study protocol will be available at the Australian New Zealand Clinical Trials Registry (ANZCTR). Any amendments to the protocol will be provided to the ANZCTR and will also be communicated to all trial researchers.

## Abbreviation

cRCT: Cluster-randomised, controlled trial
